**Trial registration number:**

NCT05577026.

STRENGTHS AND LIMITATIONS OF THIS STUDYThis cluster randomised trial evaluates a brief, scalable intervention comprising an educational seminar, written materials and feedback on opioid prescribing over 12 months.The intervention is delivered at the level of the primary healthcare centre (PHCC), targeting prescribing practices among primary healthcare professionals and reinforcing adherence to clinical guidelines.A two-year preintervention period and a 36-month postintervention follow-up allow for robust analysis of long-term prescribing trends.Inclusion of three PHCC groups (intervention, active control and observational reference) enhances internal validity and enables differentiation between intervention effects and secular trends.The trial is conducted among PHCCs in Stockholm that opted into participation, which may limit generalisability; however, the inclusion of an observational reference group supports broader contextual interpretation.

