### Participant timeline

The duration of the intervention was 12 months from the date of the seminar visit, which was defined as the baseline date. Data on opioid prescriptions will be collected over a five-year period: two preintervention years prior to baseline and three years after baseline (figure 1). PHCC enrolment began in spring 2023, and seminar visits were conducted between June 2023 and February 2024. The final data extraction is planned for 36 months after the final seminar visit.

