### Sample size

The outcome will be measured at the cluster level, using aggregated prescribing data for all registered patients at each PHCC. It was estimated that a minimum of 24 PHCCs per group were required to detect a 10% change in opioid prescribing between intervention and active control clinics. The calculation was based on a cluster-level regression analysis comparing change scores between groups, adjusted for baseline prescribing. Assumptions included 80% power, a two-sided significance level of 5%, and one covariate correlated with the outcome (r=0.39).

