#### Analyses of primary and secondary outcomes

Analyses of primary and secondary outcomes will be conducted at the PHCC level, with comparisons made between the intervention group and the active control group, as well as between the intervention group and the observational reference group. Patients registered at the PHCCs at any point during the 12 months before and 12 or 24 months after the intervention will be included in the analyses.

The number of dispensed DDDs of opioids and the number of patient-months (ie, the number of months during which patients are registered at a given PHCC) will be summarised for each PHCC. The change in DDDs per patient-month from baseline to follow-up will be calculated for each PHCC.

The difference in change between the groups will be estimated using linear regression, with baseline prescribing (DDDs per patient-month) and the matching variables accounted for in the analysis. Cluster effects at the patient level will not be adjusted for, as the unit of analysis is the PHCC. The assumption of normality will be assessed by inspecting the model residuals. Estimated effect sizes will be reported with p values (two-sided, α=0.05) and 95% CIs. A sensitivity analysis using morphine milligram equivalents may be used as a complement to DDDs to account for potency differences between opioid substances. Exploratory subgroup analyses based on characteristics of patients at participating PHCCs may also be conducted.

Cluster-level analyses will be based on register data from regional healthcare databases, which have full coverage of prescription data; missing data are not anticipated.

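### Two pre-intervention years are extracted, but the primary regression adjusts for one baseline rate; adding the earlier year as a covariate would be a nearly free gain in precision

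*Protocol article*

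**What the plan says.** The Participant timeline sets the data window at "two preintervention years prior to baseline and three years after baseline". The strengths and limitations box presents this as an asset: "A two-year preintervention period and a 36-month postintervention follow-up allow for robust analysis of long-term prescribing trends".

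Under Analyses of primary and secondary outcomes, the unit of analysis is the PHCC. The change in DDDs per patient-month is regressed on group, "with baseline prescribing (DDDs per patient-month) and the matching variables accounted for in the analysis". The same section includes patients registered in the 12 months before and the 12 or 24 months after the intervention. The article does not define the window of the baseline rate separately; 12 months is the natural reading of that inclusion sentence.

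The Sample size section rests on the same kind of model, a "cluster-level regression analysis comparing change scores between groups, adjusted for baseline prescribing", with "one covariate correlated with the outcome (r=0.39". It concludes that "a minimum of 24 PHCCs per group were required to detect a 10% change in opioid prescribing between intervention and active control clinics". It gives no standard deviation and no year-to-year correlation.

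**The concern.** With about 24 clusters per group and recruitment finished, covariates are one of the few remaining sources of precision. One year's rate measures a PHCC's usual prescribing level with error. If PHCCs differ in lasting ways, for example in patient mix or routines, the year before that carries further information on the same level, and adjusting for both years leaves a smaller residual variance. The earlier year is already in the extraction and was recorded before baseline, so it cannot bias the randomised comparison. What is at stake is the width of the confidence interval and the power for the 10% difference, not the validity of the estimate.

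**Working it through.** **Inputs from the article.** 24 PHCCs per group; target difference 10%; two-sided 5%; 80% power; one covariate with r = 0.39 (Sample size). Two pre-intervention years (Participant timeline). One baseline rate plus the matching variables in the model (Analyses of primary and secondary outcomes).

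**Inputs that must be assumed.** The correlations between yearly PHCC rates, with equal variances across years.

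**The plan's own figure.** With no SD stated, 24 per group cannot be reproduced independently. It can be back-solved: n = 2(1.96 + 0.84)² × SD²(1 − 0.39²) / 0.10² gives 24 when the SD of the change is about 13.4% of mean prescribing (about 13.1% with a t reference). The steps below do not need this SD. They start from the stated 80% and scale the residual variance.

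**Step 1: what the earlier year adds.** Regressing change on baseline has the same residual as regressing the follow-up rate on baseline. Let *a* be the correlation between adjacent years and *b* the correlation between years two apart. The partial correlation of year -2 with follow-up, given year -1, is

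p = (b − a²) / (1 − a²),

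and the residual variance is multiplied by 1 − p². With equal correlations (a = b = ρ) the multiplier is (1 + 2ρ) / (1 + ρ)². Under AR(1), b = a², so p = 0.

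**Step 2: what r = 0.39 can say about ρ.** The article gives r no sign and does not define it beyond the phrase quoted. If it is the size of the correlation between baseline and change, equal variances give r² = (1 − ρ)/2. Then ρ = 1 − 2 × 0.39² = 1 − 0.304 = 0.70.

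**Step 3: power.** With 1.960 + 0.842 = 2.802 at the design point, new power = Φ(2.802/√(1 − p²) − 1.960).

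| Assumed yearly correlations | p | Variance multiplier | Power | Gain |
|---|---|---|---|---|
| AR(1), any a | 0 | 1.00 | 80.0% | 0 |
| 0.70 one year apart, 0.60 two apart | 0.22 | 0.95 | 81.8% | about 2 points |
| 0.90 one year apart, 0.85 two apart | 0.21 | 0.96 | 81.7% | about 2 points |
| Equal, ρ = 0.70 | 0.41 | 0.83 | 86.7% | about 7 points |
| Equal, ρ = 0.90 | 0.47 | 0.78 | 88.9% | about 9 points |

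At equal ρ = 0.70 the gain is equivalent to about 24/0.83 = 29 PHCCs per group.

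**Step 4: the cost in degrees of freedom.** With group and one covariate, 48 PHCCs leave 48 − 3 = 45 degrees of freedom. Holding the noncentrality at the value that gives 80.0% there, a covariate that explains nothing lowers power to 79.96% (44 df), and a missing indicator as well to 79.92% (43 df). If the 24 pairs were fixed effects, 48 − 24 − 2 = 22 would remain. Power at the same noncentrality would then be 78.1%, falling to 77.9% with one further covariate and 77.7% with two.

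**The case against.** The strongest reply is that nothing here is wrong. The planned regression is valid, matches the model behind the sample size and already includes the matching variables. The 12-month baseline window is inferred, and finer covariate detail may sit in an analysis plan not shown. All of this stands, and it is why the point is one of efficiency. It does not remove the point: the article names the covariates of its primary model, and the earlier year is not among them.

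It is also fair that the gain may be small or nil. Prescribing is declining (Introduction), and correlation may weaken over longer lags. The cost exceeds one degree of freedom if a missing indicator is used, and any change to the primary model after the seminars have taken place must be dated and justified.

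Three stronger readings are tempting, and the article does not support them:

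- **That the trial throws the earlier year away.** The strengths and limitations box assigns the two-year period to long-term trends. It is simply not used in the primary model.
- **That selecting high-prescribing PHCCs biases the result.** Regression to the mean acts on both randomised groups alike, and baseline adjustment deals with chance imbalance.
- **That a gain of about 9 points, or power below the planned 80%, follows from the plan's figures.** The first needs equal yearly correlations of about 0.9. With equal variances that implies a baseline-change correlation of about √(0.1/2) = 0.22, not 0.39. The second needs an SD and a method of calculation that the article does not state.

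**Conclusion.** The point holds as a low-cost improvement to a valid analysis. The primary model uses one baseline rate where two years of data will be available. Including the earlier year would raise power from a nominal 80% by 0 to about 7 points on the correlation structures that sit most easily with r = 0.39, and by about 9 points only if yearly correlations are equal and near 0.9. The figure of 7 points rests on three assumptions: r = 0.39 is the baseline-change correlation, yearly variances are equal, and the correlation does not weaken between one and two years. AR(1) decay is the case with no gain. The observation about the model is secure, subject to the inferred baseline window; the size of the gain is not.

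**What to change.** Before outcome data are analysed, prespecify the PHCC's rate for months -24 to -13 (DDDs per patient-month) as an additional covariate in the primary regression, beside the existing baseline rate and the matching variables. State explicitly that the existing rate covers months -12 to -1, if that is the intention. The year-to-year correlation can be estimated from pre-intervention register data alone, which would show the likely gain without touching outcomes.

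Because Table 1 admits PHCCs that have operated for 12 months, add a simple rule for those open less than 24 months: use the months available, with a missing indicator only if some PHCC has none.

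This needs no new data and no further recruitment. It costs one degree of freedom, or two with the indicator: under 0.1 point of power with about 45 degrees of freedom, and about 0.2 points per added term if pairs are fitted as fixed effects. The change should be recorded as a dated amendment to the analysis.

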### Observational reference group

PHCCs in the observational reference group are not randomised, receive no study intervention and continue with usual care practices.

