### Randomisation and blinding

#### Allocation to the intervention or the active control group

Consenting PHCCs will be enrolled on a rolling basis and randomised in a 1:1 parallel design to either the intervention or active control group. Randomisation will be pairwise, stratified by PHCC size, using computer-generated random numbers. PHCCs unmatched due to uneven numbers at a given time point will be carried forward to the next randomisation date, and any remaining unmatched PHCCs will be randomly allocated to either group.

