#### Assignment of baseline dates

PHCCs in the active control and observational reference groups will be assigned baseline dates to match intervention PHCC seminar visit dates. This ensures temporal alignment across groups and allows the leaflet to be sent to active control PHCCs on the same date as their corresponding intervention PHCCs.

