#### Regional healthcare databases

VAL is the name of the centralised data warehouse for monitoring healthcare utilisation in Region Stockholm.^37^ The regional healthcare databases in VAL include comprehensive healthcare records on all residents, including the PHCCs at which patients are registered, inpatient and outpatient visits, and prescriptions.

Data on the study population will be extracted from the databases for the five-year study period. At the level of the PHCC, variables include ownership type (public or private sector) and sociodemographic classification. Patient-level variables include data on PHCC registration, sociodemographic characteristics (eg, age, sex, Mosaic socioeconomic classification), and healthcare utilisation (eg, prescriptions, diagnoses and visit types).

Opioid prescribing will be quantified using dispensed DDDs, a WHO standard measure based on the assumed average maintenance dose for a drug’s main indication in adults,^38^ which is available in VAL. Key data to assess study outcomes include PHCC registration, prescribing PHCC, opioid ATC code, dispensation date, DDD per package, and the number of packages dispensed. Variables that will be used in the analysis of primary and secondary outcomes are listed in table 3. Additional variables such as migration events and date of death may also be included.

**Table 3 T3:** Variables and descriptions from the regional healthcare databases (VAL) used to assess primary and secondary outcomes

Variable	Description
Registered patients per PHCC	Calculated from the number of individual registered patients at a PHCC each calendar month
Size of PHCC	Classification of PHCC size calculated from the number of registered patients: small (<5500), medium (5500–8500) or large (>8500)
PHCC registration	PHCC name, where a patient is registered each calendar month
ATC code	Seven-digit ATC code identifying the opioid substance prescribed
Prescribing PHCC	Name of the prescribing PHCC
Dispensation date	Date opioid was dispensed
Package DDD	DDDs per package dispensed
Number of packages	Number of packages dispensed

ATC, Anatomical Therapeutic Chemical; DDD, defined daily dose; PHCC, primary healthcare centre.

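### The non-randomised intervention-versus-reference comparison uses the randomised comparison's covariates, so extracted practice and patient characteristics tied to a different prescribing trend are not adjusted for and may bias it

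*Protocol article*

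**What the plan says.** Under Analyses of primary and secondary outcomes, the Protocol article compares intervention with active control "as well as between the intervention group and the observational reference group". One linear regression of each PHCC's change in DDDs per patient-month is given for both, "with baseline prescribing (DDDs per patient-month) and the matching variables accounted for in the analysis". Results carry two-sided p values at 0.05 and 95% CIs. No separate model is stated for the second comparison.

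The matching variables are not defined. Two sections bear on them. Allocation to the intervention or the active control group says "Randomisation will be pairwise, stratified by PHCC size, using computer-generated random numbers". Assignment of baseline dates says "PHCCs in the active control and observational reference groups will be assigned baseline dates to match intervention PHCC seminar visit dates". On the third group, the article states "PHCCs in the observational reference group are not randomised, receive no study intervention and continue with usual care practices".

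Under Regional healthcare databases, the PHCC-level "variables include ownership type (public or private sector) and sociodemographic classification". At patient level the extract holds "sociodemographic characteristics (eg, age, sex, Mosaic socioeconomic classification), and healthcare utilisation (eg, prescriptions, diagnoses and visit types". The same section then states: "Variables that will be used in the analysis of primary and secondary outcomes are listed in table 3". Table 3 lists registered patients, PHCC size, PHCC registration, ATC code, prescribing PHCC, dispensation date, package DDD and number of packages. Ownership, sociodemographic classification, age, sex and Mosaic class are not among them. Patient characteristics enter the outcome analyses only as optional exploratory subgroups.

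**The concern.** Baseline prescribing plus the design variables is a sound covariate set for a randomised comparison, because randomisation balances the rest in expectation. The reference comparison has no such protection. The randomised PHCCs agreed to take part, whereas the reference PHCCs are followed through registers without consent. If the two kinds of practice differ in ownership or population mix, and if those features go with a faster or slower fall in opioid prescribing, the regression attributes the difference in trend to the intervention. The Introduction says that opioid prescribing is already declining, so a difference in trend is the relevant threat.

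This matters because the comparison is more than a backdrop. The Objective names the reference group as a comparator, it sits among the primary and secondary outcome analyses, and it is reported with p values. The strengths and limitations list and the Discussion say that the three-group design helps to tell intervention effects from secular trends.

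**Working it through.** **1. The covariate set against the available variables**

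| Variable | In the stated model | In Table 3 | Extracted |
|---|---|---|---|
| Baseline DDDs per patient-month | yes | its components | yes |
| PHCC size | apparently, as a matching variable | yes | yes |
| Baseline date | possibly, as a matching variable | no | set by design |
| Ownership type | no | no | yes |
| Sociodemographic classification | no | no | yes |
| Patient age, sex, Mosaic class | no | no | yes |

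The entries for size and baseline date are inferred from the two sections on allocation and baseline dates.

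**2. The scale of random error**

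Sample size gives 24 PHCCs per group, a 10% change, 80% power, two-sided 5% and r = 0.39. It gives no SD of change, so 24 cannot be reproduced, only solved backwards. The 10% is taken here as 10% of the mean rate.

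- Normal approximation: standardised effect = √(2 × (1.960 + 0.842)² / 24) = 0.809. Residual SD = 10 / 0.809 = 12.4%. SD of change = 12.4 / √(1 − 0.39²) = 13.4%.
- Noncentral t with 45 degrees of freedom: residual SD 12.1%, SD of change 13.1%.

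As a check with the normal formula, an SD of change of 13% gives n = 23, 13.4% gives 24 and 14% gives 27.

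**3. Bias from one omitted binary factor, such as ownership**

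Bias = (difference between groups in prevalence of the factor) × (difference in 12-month change between its levels). The documents give neither input, so both are assumed. The false-positive rate at nominal 5% is for 24 versus 24 PHCCs, with SE = 12.1 × √(2/24) = 3.49 points.

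| Imbalance | Trend gap (points) | Bias (points) | False-positive rate |
|---|---|---|---|
| 10% | 2.5 | 0.25 | 5.1% |
| 20% | 5 | 1.0 | 5.9% |
| 20% | 10 | 2.0 | 8.7% |
| 30% | 10 | 3.0 | 13.4% |
| 40% | 10 | 4.0 | 20.2% |

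The size of the reference group is not stated. A larger group makes the same bias more visible: with 57 reference PHCCs the SE is 12.1 × √(1/24 + 1/57) = 2.94, and with 150 it is 12.1 × √(1/24 + 1/150) = 2.66. Simulations of 6,000 trials with 24 intervention PHCCs and 57 or 150 reference PHCCs (both assumed) gave false-positive rates of 6.3% and 6.6% at a bias of 1 point, 9.4% and 10.7% at 2 points, and 15.9% and 17.6% at 3 points. Adjusting for the factor brought them to 4.6% to 5.1%. That last result is expected by construction, since the simulated confounder is the one adjusted for.

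**4. Cost of more covariates**

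With 24 versus 24 and the residual SD held at 12.1%, the loss of degrees of freedom takes power from 80.0% with one covariate to 79.9% with three, 79.8% with five and 79.7% with eight. If a covariate is imbalanced, adjustment also widens the interval. For 70% versus 40% in equal groups, the squared correlation of group with factor is 0.25 × 0.30² / (0.55 × 0.45) = 0.091, so the SE rises by a factor of 1 / √(1 − 0.091) = 1.05 before any gain from explaining outcome variance.

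**The case against.** Five arguments stand on the other side.

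- **The outcome is a change score adjusted for baseline.** Differences that are stable over time and additive on the DDD scale cancel. This is right: only factors tied to a different trend can bias the estimate.
- **No confounding is demonstrated.** A reader might infer that the reference estimate is known to be biased. The documents do not support that. They give no comparison of the groups on ownership or patient mix and no trend by either. The 3-point scenario needs a 30-point imbalance together with a one-year trend gap as large as the whole target effect.
- **The article is condensed.** The matching variables are undefined and may already include baseline date, and how reference PHCCs are chosen is not described. It would go too far to say that they are aligned on baseline date alone. The covariate set itself is a different matter: the model sentence and Table 3 state it, so it is not merely left to a fuller document.
- **The comparison is contextual.** The Abstract says so, and the sample size concerns intervention versus active control only. A reader might infer that the claim about secular trends fails, but it is made for the three groups together, and the randomised active control already supplies that separation. The contextual label still sits uneasily with p values and with the Objective.
- **Adjustment cannot remove unmeasured differences from volunteering.** This is true, and is a reason to label the comparison as supportive as well as to adjust it.

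**Conclusion.** The point holds as a minor to moderate one. The stated model carries the randomised comparison's covariates over to a non-randomised comparison, and leaves out measured characteristics that the trial will already hold. Differences in these that go with a different prescribing trend are not adjusted for and may remain. The possible bias, 0.25 to 4 points against the 10% target for one factor, rests wholly on assumed imbalances and trend gaps. At the low end it is negligible and at the high end material, and its direction is unknown. The false-positive rates rest further on the back-solved SD and on assumed group sizes. Nothing here touches the randomised intervention-versus-control result, and a reader should not infer that the primary analysis is compromised.

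**What to change.** In Analyses of primary and secondary outcomes, give the intervention-versus-reference comparison its own prespecified adjustment set, all measured before baseline:

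- baseline prescribing and PHCC size;
- baseline date, if the matching variables do not already include it;
- ownership type and sociodemographic classification;
- the age, sex and Mosaic mix of registered patients.

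Report the minimally adjusted result beside it, and describe the comparison as supportive because unmeasured differences from volunteering remain. Define the matching variables in the same place, and add the extra covariates to Table 3. Leave the randomised model unchanged.

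The cost is a sentence or two of wording and a few degrees of freedom in this comparison only, plus a modestly wider interval if the groups turn out imbalanced. The characteristics to be added are already in the planned VAL extract. The set should be fixed before outcomes are examined: allocation is known to the study team, and covariates chosen after the results are seen would carry less weight.
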